### Research Design

Although deterioration in a control condition can take place [42], Steinert et al [43] conducted a meta-analysis and found only small changes in the WLC groups during short-term wait periods for clients with SAD in RCTs. Thus, this study adopts a WLC group design to conduct a 3-arm RCT as shown in Table 1.

There were 2 experimental groups that joined either the web-based or app-based iCBT program (Ease Online). The WLC group received the app-based treatment immediately after the 2 experimental groups completed the program. All 3 groups completed the same web-based questionnaire at pretest, posttest, and 3- and 6-month follow-ups. The WLC group completed the questionnaire one more time at posttest after the 2 experimental groups completed the program. To increase the submission rate of questionnaire, participants were given 2 more weeks to submit an email questionnaire after the submission deadline in the program system. The RCT was conducted in cohorts for implementation feasibility. Specifically, in each cohort, around 30 qualified participants were randomized into one of the 3 groups through computer-generated random numbers, with approximately 10 in each group. The program evaluators were blinded to the allocation of the participants. The participant recruitment flowchart is shown in Figure 1.

**Table 1 table1:** Participant group design.

Groups	Research design						
Web-based	O^a^	X^b^	O		O	O	N/A^c^
App-based	O	X	O		O	O	N/A
Waitlist control	O		O	X	O	O	O

^a^O: test.

^b^X: intervention.

^c^N/A: not applicable.

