### Intervention: the Ease Online Program

The Ease Online program is 14 weeks in duration. The program adopts a blended mode of service delivery as guided self-help iCBT has demonstrated lower attrition than nonguided self-help iCBT [18], and therapist contact has been found to be a significant predictor of retention and outcomes [23]. The program consists of 9 web-based modules and 5 individual counseling sessions (including 2 VRET sessions). The program contents were developed on the basis of the CBT model developed by Beck [44] and CBT delivered to Chinese clients by Wong [45] and Pan and Zhuang [46]. Specifically, a variety of cognitive behavioral skills for coping with social anxiety are introduced in the 9 web-based modules, each with a specific theme. The themes of the nine web-based modules are (1) recognizing your social anxiety responses, (2) identifying automatic thoughts and cognitive distortions, (3) self-talk and positive statements, (4) behavioral experiment, (5) fear hierarchy, (6) exposure therapy, (7) identifying cognitive rules, (8) relaxing dysfunctional cognitive rules, and (9) saying bye-bye to social anxiety. The CBT skills are briefed and debriefed by using an animation video and demonstrated through 4 case videos. Each web-based module starts with a mood check for social anxiety in the past week and ends with a session review and an assignment that helps clients to apply the learned skills to cope with their own social anxiety. Other components of the program include therapist feedback on assignments, internal messages, forums, client portfolios, web-based questionnaires, reminders, and web-based bookings. An introduction video of the program provides a navigation on all of the program components after the clients log into the system. The client platform has a web-based version in which clients can log into the program website or a mobile app that can be downloaded through Google Play or Apple Store. After being randomized into the program, clients were provided an account to log into the system. Clients who are assigned a PC web account cannot log in through the app and vice versa. All clients were assigned to a therapist who not only provided web-based feedback on their assignments and responded to their private messages, but also offered 5 individual counseling sessions that monitored the progress of the clients and addressed any challenges that the clients encountered when working on the web-based modules. There is also a backstage management platform for the therapist, which offers different functions including creating cohorts, managing bookings and forums, providing feedback on client exercises, monitoring client progress, etc. The therapist helped the clients understand and review the module contents and apply the CBT skills into their own situations in 5 individual counseling sessions that were conducted either in person or on Zoom or WhatsApp.

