
A VR system for exposure therapy has also been developed for this program, which includes 5 virtual scenarios: (1) interviewing for a job, (2) delivering a presentation, (3) participating in work performance evaluation, (4) expressing disagreement, and (5) drinking in public. The VR system uses an 180° video of real humans. There is a storyline for each VR scenario and a couple of interactions between the client and the VR environment, which are guided by a prerecorded voice-over. The clients wear a head-mounted display and respond by moving their head. The voice responses of the clients are recorded in the VR system for replay. The technologies used for the development of the VR system include voice recording, VR180 stitching, VR game engine development, VR motion tracking on the target point, and an auto-trigger based on the user’s headset direction. An administration control panel has been developed for the therapist to control the VR interaction. In the beginning of each VRET session, the therapist provides a short briefing and asks the client to choose one VR scenario. Then, the client participates in the VRET for no longer than 15 minutes. The therapist then proceeds to debrief the client upon completion of each VRET session and submits a session report on the Ease Online system. Examples of VRET photographs are shown in Figure 2.

The program sessions outlined in Table 2 are released to the client on a weekly basis. The treatment schedule is programmed into the Ease Online system. Progress is recorded as a score when the client completes a task, and a total score is calculated as the total progress. All of the program videos are tailored for Hong Kong people and developed from local cases. The Cantonese language is used in the program. To ensure data security and privacy, 2-factor authentication is adopted when logging in with a password that is preset by the user and a one-time password sent to his/her email address. All of the collected electronic data are encrypted. The program is hosted on the server of the Information and Technology Office of the university where the author is employed. Before the program launched, a user acceptance test was conducted by the author and project staff, and bugs were fixed accordingly by the programmer of this project.

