### Outcome Measures

#### Primary Outcome Measures

The Chinese version of the SPIN [37,47] was used to assess the severity of social phobia symptoms. The measure consists of 17 items with 3 subscales: fear, avoidance, and physiological response. Participants were asked to rate their distress for each symptom during the past week on a 5-point Likert scale that ranges from “0” (not at all) to “4” (very much so). All of the item scores were summed up into a total score that ranged from 0 to 68, with a higher score indicating a higher level of anxiety. Sample items included “fear of others watching,” “avoid talking to others,” and “feeling bothered by blushing.” The α coefficient is .89 for the Chinese version of the SPIN [37].

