### Limitations

There are several limitations of this study that should be considered. First, only completed tasks are recorded in the system, but there are no records of therapist time and use time of the client in the system. User time can be recorded in the system in future research to calculate the average therapist time spent and the amount of time for which the clients use the system. Second, the number of missing data at posttest and follow-up is quite high—this may be related to the busy lifestyle in Hong Kong and nature of free services provided in this study, although various means including email and phone calls have been used to remind clients to complete the web-based questionnaires after the intervention. Different approaches need to be used in future research to increase the response rate of postintervention assessments. Third, although several strategies are adopted ensuring compliance with the intervention, future research may include independent ratings by certified cognitive behavioral therapists of a random selection of the progress reports of the individual counseling and VRET sessions as well as assignment feedback. Fourth, participants are mainly recruited via open recruitment, which may cause recruitment difficulties and a high nonresponse rate after enrollment. Collaboration with local social service sectors is suggested in future research for participant recruitment and follow-up with service delivery and data collection. Fifth, in the VR system, 180° videos are produced, which may limit the view of clients in the VR environment. Future research may aim to develop 360° videos for the VRET system. Finally, 5 VR scenarios are developed in this study; future research may aim to develop more VR scenarios to allow clients to choose social situations that are more relevant to them.

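### As written, a waitlist control posttest can be returned after waitlist treatment has begun, because treatment start, posttest and the two-week grace period are not reconciled

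*Protocol article*

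**What the plan says.** All timing statements are in the protocol article, mostly under Research Design.

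- Start of waitlist treatment: "The WLC group received the app-based treatment immediately after the 2 experimental groups completed the program". The abstract agrees in substance.
- Control posttest: "The WLC group completed the questionnaire one more time at posttest after the 2 experimental groups completed the program".
- Grace period: "participants were given 2 more weeks to submit an email questionnaire after the submission deadline in the program system". The stated purpose is a better submission rate. No arm or assessment is excepted, and the system deadline itself is not given.
- Table 1 ("Participant group design") sets out the waitlist arm as test, test, intervention, then three further tests. The second test therefore precedes the intervention.

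Two further statements bear on the point. Under the intervention heading, "The program sessions outlined in Table 2 are released to the client on a weekly basis", and Table 2 puts modules 1 and 2 in weeks 1 and 2. For the primary outcome, SPIN, "Participants were asked to rate their distress for each symptom during the past week".

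**The concern.** The second waitlist test is the only untreated measurement after baseline. The waitlist pretest is also untreated, but every later waitlist test follows treatment. The randomized comparison with a control condition therefore rests on this one assessment.

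In the experimental arms a late posttest only lengthens the interval since treatment ended. In the waitlist arm it can change the condition being measured, from untreated to early treatment. If early treatment helps at all, such scores lower the control mean and shrink the between-group difference.

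The planned handling of missing data gives no protection. Under Data Analysis, multiple imputation is for missing values, and a late score counts as observed. It would enter the intention-to-treat analysis as an ordinary control value.

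**Working it through.** The plan gives no figure to reproduce. The check is a timeline, followed by an illustration of size on assumed values.

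**Timeline**

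1. Let T be the day the experimental arms finish. Waitlist treatment opens at about T (Research Design).
2. The control posttest is taken after T (Research Design). Let its system deadline be T + D. D is not stated. Since the test follows T, I take D ≥ 0 days.
3. A grace-period return arrives between T + D and T + D + 14 days.
4. Time on treatment at a grace-period return is therefore between D and D + 14 days. With D = 0 the maximum is 2 of the 14 program weeks, 2/14 = 14%. With D > 0 it is longer, and some returns made before the deadline would also follow T.
5. With weekly release, two weeks covers modules 1 and 2 (Table 2).
6. SPIN looks back 7 days. For a return x days after the deadline, the treated share of the recall week is min(7, D + x)/7. With D = 0 this is 3/7 = 43% at x = 3 and 100% from x = 7 onward.

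Set beside Table 1, which has the second waitlist test before the intervention, the prose permits the reverse order.

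**Illustration of size**

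Let q be the share of waitlist posttests answered after treatment began, and g the share of the full benefit reached by then. If late and punctual respondents are otherwise alike and the standard deviation is unchanged, the control mean moves by q × g of the full effect, so

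retained contrast = 1 − q × g.

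The documents give neither q nor g. All values below are assumptions.

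- q = 10%, g = 10%: 0.10 × 0.10 = 1% understatement.
- q = 30%, g = 30%: 0.30 × 0.30 = 9% understatement.
- Wider range, low end: q = 10%, g = 1/14 (one week, benefit proportional to time): 0.10 × 0.071 = 0.7%, so 99.3% is retained.
- Two weeks, benefit proportional to time, g = 2/14: 1.4% at q = 10%, 3.6% at q = 25%, 7.1% at q = 50%.
- Wider range, high end: q = 50%, g = 30%: 0.50 × 0.30 = 15%, so 85.0% is retained.

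Over the wider range, an assumed standardized difference of 0.80 would be seen as 0.80 × 0.993 = 0.79 down to 0.80 × 0.85 = 0.68.

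**The case against.** The strongest reply is that the overlap is possible, not shown. The system deadline is unstated, Table 1 gives the intended order, and the article condenses a fuller protocol. If access was in practice held until the posttest came back, the problem disappears. That stands, and it limits the point to what the text permits. It does not dispose of it, because the article states rules which, applied together, contradict its own design table.

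A second reply is that little treatment could have been received. Table 2 schedules the first counseling session in week 4, the behavioral experiment in week 5, the exposure module in week 7 and virtual reality exposure in weeks 9 and 10. Two weeks would cover two introductory modules and perhaps written feedback or messages. This also stands: a reader might infer that late respondents had already had a counseling session, and with a two-week overlap the schedule does not support that. It makes the upper values of g hard to defend.

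Third, the bias runs toward no difference, so this mechanism would not by itself produce a false claim of benefit. That is right if early treatment helps.

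Fourth, discarding observed control scores has its own cost. Limitations says that "the number of missing data at posttest and follow-up is quite high", and late returns are unlikely to be a random subset. That argues for showing results with and without these scores, not for deletion alone.

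**Conclusion.** The point holds as a conflict between stated rules. As written, a waitlist control posttest can be returned after waitlist treatment has begun, contrary to the order in Table 1, and nothing stated separates such scores from untreated ones.

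A reader might go further and infer that late control posttests were in fact taken on treatment, or that the control comparison is invalid. The documents support neither. They give no system deadline, no number of late returns and no dates of access. High missingness at posttest is reported, but that is not a late rate.

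The size is unknown and probably modest. It is 1–9% understatement if q and g each lie between 10% and 30%, and 0.7–15% over the wider assumed range. The direction, toward no difference, assumes that early treatment helps. The data needed to settle the matter may already exist, and the article describes the main analysis in the future tense, with data collection still running.

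**What to change.** 1. **Text.** Reconcile the Research Design statements on waitlist treatment start, control posttest timing and the grace period with each other and with Table 1, so that the control posttest precedes access to treatment content. State the system deadline.
2. **Data already collected.** For each waitlist participant, compare the date the control posttest was submitted, or received by email, with the date treatment content was first released to, or first completed by, that participant. Check all returns, not only those in the grace period. First log-in is not a usable marker: punctual questionnaires are answered in the program system, so logging in need not mean treatment, late ones arrive by email, and no log-in time stamps are described. Completed tasks are recorded. Report the count. If it is zero, saying so closes the matter.
3. **Analysis.** Before analysis, pre-specify one analysis that sets waitlist posttests dated after first access to content to missing under the planned multiple imputation, and show it alongside one that keeps them.

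The cost is a date check, a few sentences and some additional imputed control values. Their number depends on the unknown late rate: at an assumed 10–30% late, with all 110 planned waitlist posttests returned, it would be 0.10 × 110 = 11 to 0.30 × 110 = 33. Imputation may not fully correct for late respondents differing from punctual ones, which is why both results should be shown.

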## Introduction

### Background

Social anxiety symptoms have increased significantly during the COVID-19 pandemic [1]. Social anxiety disorder (SAD) is one of the most common mental health problems, yet few seek treatment [2]. Individuals with SAD experience excessive fear and anxiety during social interactions, which is disproportionate to the social situation itself. SAD often involves negative evaluation and rejection by others and a constant fear of embarrassment or humiliation [3]. Therefore, individuals with SAD often avoid social interactions, which may have detrimental impacts on most areas of life, including their career, education, social relationships, and mental health [4]. Social anxiety usually emerges during performance situations (such as job interviews, public presentations, or attending a meeting) and interpersonal situations (such as greeting someone, drinking and eating in public, taking part in social gatherings, or shopping). In Hong Kong, the 12-month prevalence rate of SAD is reported to be 3.2% [5], which translates into an estimated 230,000 cases. However, only 8.7% of people with SAD in Hong Kong had previously sought treatment [5].

People with SAD face certain treatment barriers that prevent them from seeking mental health services, including fear of judgement, uncertainty of the resources for receiving help, and skepticism regarding anxiety disorders [6]. In Hong Kong, the barriers also include the social and self-stigmas of mental illnesses, long waiting lists for public health care, and exorbitant costs of private treatment. However, people with SAD consider the internet as a good social outlet, which not only helps them to alleviate their fear during general social interactions but also meets their social needs [7].

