### Sample Size

The sample size was calculated by using a computer program called G*Power (version 3.1.5; Universität Düsseldorf). The statistical method used was a multivariate ANOVA with repeated measures (within-between interactions). The effect size was assumed to be 0.40 (large) [40]. The number of groups was 3 (2 experimental groups and 1 control group) and 7 measures applied (please see the *Outcome Measures* section). The α value was set at .01. The calculations resulted in a minimum sample size of 139. This study aims at recruiting 330 eligible participants, with 110 in each experimental group and the waitlist control (WLC) group, respectively.

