### Data Analysis

Intent-to-treat analysis, which is the least biased way to estimate an intervention’s effects [57], was used for data analysis. Missing data will be managed using multiple imputation [58]. Multivariate ANOVA with repeated measures will be performed to test the intervention’s effectiveness on continuous variables over time. Time (pretest, posttest, and 3- and 6-month follow-ups), condition (web-based iCBT, app-based iCBT, and WLC), and the interaction of time-by-condition will be specified as the categorical fixed factors. Medication and demographic factors (eg, gender, age, and marital status) will be specified as fixed covariates to control the potential confounding effects. Cohen *d* will be calculated as the index of the effect size both within and between groups.

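### Participants are randomised within cohorts of about 30, but the stated repeated-measures model leaves cohort out, which can cost some precision without biasing the design

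*Protocol article*

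**What the plan says.** Research Design states that "The RCT was conducted in cohorts for implementation feasibility" and that "in each cohort, around 30 qualified participants were randomized into one of the 3 groups through computer-generated random numbers", "with approximately 10 in each group". Sample Size sets a target of 330, or 110 per arm.

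Data Analysis plans the following: "Multivariate ANOVA with repeated measures will be performed to test the intervention’s effectiveness on continuous variables over time". Time, condition "and the interaction of time-by-condition will be specified as the categorical fixed factors". On covariates it says: "Medication and demographic factors (eg, gender, age, and marital status) will be specified as fixed covariates to control the potential confounding effects". Between-group Cohen *d* is also planned, and missing data are to be multiply imputed.

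Cohort appears in neither the list of factors nor the list of covariates. The examples in the covariate sentence illustrate demographic factors, and cohort is not one. Nowhere does the article treat cohort as a stratum, covariate or random effect.

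**The concern.** Cohort is the group within which allocation was made. If arms are balanced within cohorts, the true variance of an arm comparison excludes the differences between cohorts. A model without cohort still counts those differences as error, so its standard errors are too large and its tests lose power.

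Cohort differences are plausible. Recruitment began in January 2021 and 329 people had joined by February 2023, so cohorts may be up to two years apart. Results also lists changes to the program system among the activities since launch. The time-by-condition test would be affected only if cohorts differ in how scores move over time, and not merely in their level.

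**Working it through.** **The plan's own figure.** The minimum of 139 (Sample Size) reproduces with the Pillai-trace approximation for a within-between interaction: 3 groups, 7 measures, effect size 0.40, alpha 0.01. This gives df1 = (3−1)(7−1) = 12, df2 = 2(139−3−6+2) = 264 and λ = 139 × 2 × 0.40² = 44.48, with power 0.990. The article does not state power; 139 is the smallest N that reaches 0.99. Cohort plays no part in the calculation.

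**Inputs from the article.** Number of cohorts: 330/30 = 11, with about 10 per arm in each.

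**Assumed inputs.** The total variance at a visit is 1. A share *b* is a cohort effect constant over time, or a share *c* is a cohort effect that varies independently from visit to visit. The pre-post correlation within cohort is *r* = 0.6. Arms are exactly balanced within cohort. Each result is the standard error (SE) without cohort divided by the SE with cohort.

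**1. Unadjusted posttest comparison.** Ratio = 1/√(1−share).
- Share 0.01: 1.005
- Share 0.05: 1.026
- Share 0.10: 1.054

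**2. Pre-post change (the time-by-condition contrast), constant cohort effect.** The effect enters both visits equally and drops out of the difference, so the ratio is 1.00. In a simulation of 11 cohorts × 30 with *b* = 0.10, the SE was 0.114 with or without cohort. In a separate null simulation with the same *b*, the rejection rate at nominal 0.05 was 0.048 either way.

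**3. Pretest-adjusted posttest, constant cohort effect.** Ratio = √{[1−(b+(1−b)r)²] / [(1−b)(1−r²)]}.
- *b* = 0.05: √(0.6156/0.608) = 1.006
- *b* = 0.10: √(0.5904/0.576) = 1.012

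**4. Pre-post change, time-varying cohort effect.** Ratio = √{[2c+2(1−c)(1−r)] / [2(1−c)(1−r)]}.
- *c* = 0.01: √(0.812/0.792) = 1.013
- *c* = 0.05: √(0.86/0.76) = 1.064
- *c* = 0.05 with *r* = 0.5: √(1.05/0.95) = 1.051

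**5. Pretest-adjusted posttest, time-varying cohort effect.** Ratio = √{[1−((1−c)r)²] / [(1−c)(1−r²)]}. At *c* = 0.05 this is √(0.6751/0.608) = 1.054.

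**6. Effect on the error rate.** In a null simulation at nominal 0.05 (6,000 runs, Monte Carlo SE about 0.003; *c* = 0.05, *r* = 0.5), the change contrast rejected in 0.036 of runs without cohort and 0.050 with it. The test without cohort is conservative.

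**7. Cost of inclusion.** Residual degrees of freedom fall from 330−3 = 327 to 317. With exact balance the SE is otherwise unchanged. With simple randomisation inside each cohort and no time-varying cohort effect, adding cohort makes the SE about 0.5–1.5% larger, of the order of √(327/317) = 1.016.

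**The case against.** The case against has real force on size.

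- **Stable cohort differences.** A reader might infer that all between-cohort variance inflates the planned test, by 2.6–5.4% for a 5–10% share. That holds only for an unadjusted posttest comparison (step 1). The planned test is time-by-condition, where stable differences cancel.
- **Balance within cohort.** The article gives approximate numbers and mentions random numbers, but it states no blocking. Under simple randomisation inside cohorts, a test without cohort keeps its level and is only less precise. Uneven arm sizes within a cohort are then chance variation; reading them as a bias from calendar time is not supported.
- **The pandemic remark.** "Social anxiety symptoms have increased significantly during the COVID-19 pandemic" says nothing about change between January 2021 and February 2023, or about differences between cohorts. It does not show that cohort predicts outcome. The common entry limits on SPIN and BDI-II also narrow baseline differences.
- **Sample size margin.** The target of 330 is well above the stated minimum of 139, so a few per cent of SE does not threaten the trial. High missingness, reported under Limitations, erodes that margin.
- **Condensed article.** One might say that cohort was left to a fuller plan. This stands only in part, because the article does name the model terms, and they omit the variable within which it randomised.

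What survives is the mismatch between randomisation and model, with a loss confined mainly to cohort differences that change over time.

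**Conclusion.** The point holds in modest form. Allocation is within cohort and the named model does not contain cohort. The design is not biased and false positives are not inflated. The possible harm is lost precision and, with balance within cohort, a slightly conservative test.

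The size rests on a cohort variance that the documents do not give. For the time-by-condition contrast it is nil for stable cohort effects, about 1% of the SE at a 1% time-varying share and about 6% at a 5% share, with a pre-post correlation of 0.6 and exact balance assumed. The change is worth making because it is cheap and data collection was still under way at the time of the report, but the results do not stand or fall on it.

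**What to change.** Add cohort and cohort-by-time as fixed factors in the repeated-measures model. A random cohort intercept alone is not enough, because it leaves in the error term the time-varying part that affects the planned test. In any pretest-adjusted posttest comparison, add cohort as a fixed factor. Include cohort in the multiple-imputation model as well, since balance at randomisation need not carry over to those who respond. The article should also state whether allocation within each cohort was forced to balance.

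The cost is about 10 degrees of freedom per contrast out of about 327. If allocation was not balanced within cohort and cohort has no time-varying effect, the SE also rises by about 0.5–1.5%. The therapist platform is used to create cohorts, so the variable should already be on record.
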